## Results

The study began in November 2018 with the training of health professionals in the different participating centers. Then, standard operating procedures were developed following the good practice guidelines for the clinical investigation of medical devices for human participants. The first recruitment started in March 2019 in Brazil. Data collection is planned to end in December 2020, and the results should be available in March 2021.

## Discussion

### Strengths and Limitations

The novel device is expected to contribute to the risk evaluation of the newborn, adding clinical value anywhere a child is born without GA information, with focus on scenarios with a limited access to high-cost technology. GA is a trigger information in birth scenario for making decisions on the best delivery of care [6-8]. Actions for the preterm birth morbidity and mortality mitigation face the faith that GA estimate is a trivial task [31]. This study will provide evidence of the accuracy of an original method for GA calculation at birth that will be useful in settings where GA is not routinely assessed by ultrasound during pregnancy [8]. Last menstrual period dating will be estimated by interview [18] and clinical document scanning to overcome the issue of absent ultrasound dating and memory recall inaccuracies. WHO recognizes 4-As medical devices as essential to the reliable functioning of health systems. For this proposal, the framework of development gathers Available, Accessible, Appropriate, and Affordable health technologies [32]. Effective and low-cost medical devices might be a contribution to mitigating the gap between well-equipped care settings and the needy ones for the reduction of preventable newborn deaths [8,33]. The emergent technology we test in this clinical study (ie, light scan to determine skin age) is included in the WHO compendium of innovative health technologies for low-resource settings due to the potential to improve health systems in these settings [33].

Regarding the step for a new technology validation, previous reports suggested alternative approaches for postnatal GA prediction, as well as for forecasting respiratory morbidity related to preterm birth prognosis. Using some elements of the newborn screening of congenital diseases associated with birth weight, a predicting mathematical model estimated the GA with high accuracy [34]. The accuracy analyses were useful to evaluate the performance of quantitative ultrasound texture assessment in order to predict neonatal respiratory morbidity [35].

This study will also evaluate an additional step beyond the prematurity identification based on the GA, the capacity of the technology to identify immediate respiratory complications due to immaturity in the newborn. The lung maturity of a newborn is related to a deficiency of surfactant, a phospholipid essential for alveolar stability, which is affected by the chronology of gestation and factors such as maternal disease [36]. This hypothesis is based on the synchronous development of fetal organs and tissues during gestation. We expect limitations in respiratory outcome evaluations, from the chest X-ray pattern and the improvement after surfactant therapy, as these resources are not always available in low-income settings. However, we believe that GA assessed by the new device could also help to identify those newborns who need respiratory support in the target population.

The results of this clinical study have the potential to validate a new device to easily assess postnatal GA, supporting SGA identification when pregnancy dating is unreliable or unknown. The quality of information about the chronology of pregnancy at birth is critical for the detection of premature and SGA newborns, differentiating small and sick infants from those who are small but healthy [6].

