### Prior Work

The optical properties of the skin’s interaction with light can be evaluated by devices that emit and receive photons [13]. Variations in light scattering through the skin are believed to be associated with changes in skin thickness, the concentration of chromophores, and light wavelength [14]. A novel technology was developed to estimate GA at birth (Test-GA) by analyzing the photobiological properties of the newborn’s skin in combination with clinical variables [15]. This noninvasive and nonionizing technology features a probe containing light emitters and receivers that is brought in contact with the skin over the sole. A mathematical algorithm provides an estimated GA within seconds, combining the skin reflection with clinical adjusters, such as birth weight and incubator stay [15].

The timeline of the new medical device development involves sequential steps [16], represented in Figure 1. The prototype of the device previously evaluated 115 newborns at 24-41 weeks’ gestation with promising results [15]. After insights from this first clinical experiment published in 2017, the technology received improvements to mitigate external influences in the test, such as humidity, ambient light, and to ease the user handling. The current version is a small device, about the size of a pen, with an automated ability to measure skin reflection. To reduce examiner influence, the device now warns about errors of measurement. Clinical variables are presented in a digital screen immediately after the newborn skin assessment. Since February 2019, a clinical trial is taking place in 5 Brazilian hospitals to advance the GA prediction modeling, using a sample of 787 newborns [17]. The planned date of last enrollment is July 2020.

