### Present Protocol of Research

This protocol gathers data from Brazil and Mozambique referral centers. This step represents the clinical validation of the prediction model established in the preceding clinical trials. It aims to validate an optimized version of the device in low-resource birth settings, using a data set obtained in different populations, before introducing it in the market. The analysis relies on real-world antenatal GA estimations obtained during pregnancy in which first-trimester ultrasound may not always be available or reliable. The primary hypothesis of this study is that photobiological properties of the skin measured by the device, and adjusted by clinical variables, will allow the accurate prediction of GA (Test-GA) in low-birth-weight newborns.

The primary objective of this study is to validate the preemie test statistical model for GA estimation at birth and its accuracy to detect prematurity in low-birth-weight newborns. The secondary objective is to evaluate whether there is an association between skin reflection and the occurrence of early respiratory complications.

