### Eligibility Criteria and Participant Timeline

A sequential enrollment of newborns will follow the inclusion of participants based on eligibility criteria until the sample size is achieved. The inclusion criteria are liveborn infants weighing 500-2499 g with GA information obtained using a qualified last menstrual period or obstetric ultrasound <24 weeks’ gestation (Comparator-GA). Exclusion criteria are structural skin alterations or conditions that modify the skin, such as anhydramnios, hydrops, congenital skin diseases, and chorioamnionitis.

Table 1 illustrates the schedule of enrollment, test application, and endpoint measurement. The skin assessment will occur during the first 24 hours of age. The newborns will be followed up for 72 hours until discharge, held in hospital (for treatment-related purposes), or death, whichever occurs first, considered the study exit. The newborns will continue to receive standard assistance after the study follow-up according to settings, resources, and local staff definitions, whether during hospital admission or at hospital discharge or re-admission.

**Table 1 table1:** Participant timeline of the study.

Study procedures	Before Test-GA	Test-GA, ≤24 hours old	72 hours old: discharged, held in hospital, or death
Enrollment 1: Prospective cohort study^a,b^	X		
Informed consent	X		
Taking of obstetric history	X		
Intervention: Test-GA		X	
Comparator: Best estimation of GA available		X	
Enrollment 2: Nested case–control study^c^			X
Assessments and analysis^d^			X

^a^Inclusion criteria are liveborn, Comparator-GA (reliable last menstrual period [18] or ultrasound assessment at <24 weeks’ gestation [8]), birth weight (500-2499 g), and ≤24 hours old.

^b^Exclusion criteria are malformation with structural skin alterations and skin modifiers (eg, anhydramnios, hydrops, congenital skin diseases, chorioamnionitis).

^c^To determine eligibility criteria for paired allocation according to birth weight range to either the case group (TTN or RDS) or the control group (without TTN, RDS, tachypnea due to other reasons, or bloodstream infection).

^d^Neonatal outcomes including respiratory complications due to prematurity, neonatal intensive care unit admission, or ventilatory support

GA: gestational age; RDS: respiratory distress syndrome; TTN: transitory tachypnea of the newborn.

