Within the study cohort, a secondary nested case–control study will include newborns with the following inclusion criteria: (1) for the case group, respiratory distress syndrome or transitory tachypnea of the newborn; (2) for the control group, newborns will be randomly selected with no respiratory diseases or manifestations by other conditions, paired by birth weight range: <1000 g, 1000-1499 g, or 1500-2499 g.

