#### Secondary Outcomes

The secondary endpoint will be the proportion of correctly identified SGA newborns under the tenth percentile of GA according to Intergrowth 21 standards [25]. For this endpoint, the proportion of SGA newborns detected by the Test-GA will be compared with that detected by the Comparator-GA.

Others secondary endpoints in the case–control nested study will be the capacity of the Test-GA results to predict the following neonatal complications:

Respiratory distress syndrome based on clinical and radiological findings and respiratory outcomes [26,27].Transitory tachypnea of the newborn based on clinical findings and respiratory outcomes [26].Ventilatory support due to pulmonary immaturity.Neonatal intensive care unit admission for pulmonary immaturity.

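### Controls in the respiratory case–control study are paired on birth weight only; pairing within hospital or country as well would cheaply close a possible route for between-country confounding

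*Protocol article*

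**What the plan says.** The Present Protocol of Research section states that "This protocol gathers data from Brazil and Mozambique referral centers" and that validation is carried out "using a data set obtained in different populations".

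Under Eligibility Criteria and Participant Timeline, cases are newborns with RDS or transitory tachypnea (TTN). Controls are chosen at random from newborns without respiratory disease or manifestations, "paired by birth weight range: <1000 g, 1000-1499 g, or 1500-2499 g". Footnote c of Table 1 gives the same single pairing factor: "To determine eligibility criteria for paired allocation according to birth weight range". Neither place names hospital or country.

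Secondary Outcomes gives the two diagnoses different evidence: "Respiratory distress syndrome based on clinical and radiological findings and respiratory outcomes" against "Transitory tachypnea of the newborn based on clinical findings and respiratory outcomes". Only the first involves radiology. Strengths and Limitations then expects difficulty with respiratory outcomes that rest on chest X-ray pattern and response to surfactant, because "these resources are not always available in low-income settings".

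Prior Work says that variation in light scattering through the skin is thought to go with "changes in skin thickness, the concentration of chromophores, and light wavelength".

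Statistical Analysis lists ROC curves, association tests and risk ratios for the respiratory question. It does not mention site or country in either direction.

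**The concern.** Country confounds the respiratory comparison if it is related both to the reading and to the recorded case label. The protocol gives a plausible route to each. Access to X-ray and surfactant may vary by setting, which could change who is recorded as having RDS. Readings may differ between populations through chromophores. Birth weight pairing does not balance country between cases and controls, so the stated selection rule leaves that path open.

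If both links exist and the comparison is made across countries, the ROC curve and association tests would mix a between-country difference with the within-country signal that matters clinically. That could suggest an association where there is none, or weaken a real one. At stake is the secondary objective on respiratory complications, not the primary gestational age validation.

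**Working it through.** The protocol states no figure on this point, so there is none to reproduce. The check asks which links the text supports and how large the distortion could be under assumed inputs.

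**Step 1: the links**

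- *Setting to case label.* Missing X-ray bears on RDS. TTN needs no radiology and also counts as a case, so a symptomatic newborn without an X-ray may still enter the case group as TTN. Such a newborn cannot become a control. Missing radiology therefore acts mainly on the RDS/TTN split and on RDS-only results. It changes the combined case group only if such newborns fall out of both groups.
- *Setting to reading.* The text supports a dependence on chromophores and says that the populations differ. It does not say that the reading differs by country.

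**Step 2: pooled AUC with no true association**

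Assumptions (none from the documents): equal numbers per country; case fraction 50% in country A and 30% or 20% in country B; readings normal with SD 1 and a shift D of 0.5 or 1.0 SD between countries; within-country AUC 0.50; controls drawn without regard to country.

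Let p1 be the share of cases from B and p0 the share of controls from B. Then

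pooled AUC = 0.5 + (p1 − p0) × [Φ(D/√2) − 0.5]

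Here Φ(0.5/√2) − 0.5 = 0.138 and Φ(1.0/√2) − 0.5 = 0.260.

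- 50% vs 30%: p1 = 0.3/0.8 = 0.375; p0 = 0.7/1.2 = 0.583; difference −0.208. The AUC departs from 0.5 by 0.208 × 0.138 = 0.029 or 0.208 × 0.260 = 0.054.
- 50% vs 20%: p1 = 0.2/0.7 = 0.286; p0 = 0.8/1.3 = 0.615; difference −0.330. The AUC departs from 0.5 by 0.330 × 0.138 = 0.046 or 0.330 × 0.260 = 0.086.

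The pooled AUC is thus 0.529–0.586 or 0.414–0.471, depending on the sign of D.

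**Step 3: pooled AUC with a true association**

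A case shift of 0.742 SD gives a within-country AUC of Φ(0.742/√2) = 0.70. The extremes come from 50% vs 20% with D = ±1. Case–control pairs split as follows: same country 0.286 × 0.615 + 0.714 × 0.385 = 0.451; case from B with control from A 0.110; case from A with control from B 0.440.

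- D = +1: 0.451 × 0.70 + 0.110 × Φ(1.742/√2) + 0.440 × Φ(−0.258/√2) = 0.315 + 0.098 + 0.188 = 0.601.
- D = −1: 0.315 + 0.110 × 0.428 + 0.440 × 0.891 = 0.315 + 0.047 + 0.392 = 0.754.

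**Step 4: error rate of an association test**

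A separate simulation used a cohort of 298, one control per case, no true association, a two-sided 5% test and 3,000 runs per scenario. Assumed case rates were 40% in Brazil and 40% down to 10% in Mozambique, with a Mozambique share of 30% or 50%.

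- Equal rates (40%/40%): pooled AUC 0.500 and rejection about 5%, whatever the shift in reading.
- 40% vs 20% with a 1 SD shift: pooled AUC 0.549–0.562; rejection 23% (30% share) to 30% (50% share).
- All scenarios, adjusted for country: rejection 4.2–6.0%.

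Bias needs both links at once, and accounting for country removes it. None of these calculations models the birth weight pairing or the exclusion of symptomatic newborns from the controls.

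**The case against.** The strongest reply is that both links are inferred. The remark on resources concerns low-income settings in general; it does not say that any study hospital lacks X-ray or surfactant, and Study Settings describes all sites as referral centers for high-risk pregnancies and neonatal care. No text says that chromophores at the sole, where the probe is applied, differ by country. The secondary endpoint is worded as prediction by Test-GA, which also uses birth weight and incubator stay, so a shift in raw reflectance need not carry over in full. All of this stands, and it is why no size or direction can be given.

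It also stands that cases include TTN and that symptomatic newborns cannot be controls. Unequal X-ray access would not by itself produce the assumed case fractions.

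A reader might infer that Statistical Analysis pools everything across countries. It does not say so. It is silent on site, and an article may leave stratification or adjustment to an analysis plan that is not shown. What remains is the selection rule itself, which is written out in two places and names birth weight alone.

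The Discussion does disclose the resource limitation, but as a limit on outcome evaluation. It does not connect it to control selection or to the optical reading.

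**Conclusion.** The point holds as a modest design improvement. The control-selection rule omits hospital and country in a two-country study where the protocol's own text makes a relation of setting to both reading and outcome plausible, most directly for RDS-specific analyses.

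Under the assumed inputs, pooling would turn a null AUC into 0.53–0.59 or 0.41–0.47, and a true 0.70 into 0.60–0.75. These figures illustrate the mechanism; they do not estimate the bias in this study. If recorded case rates are equal across countries, or the reading does not shift, the bias vanishes.

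It would be tempting to conclude that the respiratory result could not be interpreted. The documents do not support that: neither link is established, an AUC of 0.53–0.59 would in any case be read as poor discrimination, and adjustment for country would restore the error rate even under the existing pairing.

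**What to change.** In Eligibility Criteria and Participant Timeline, and in footnote c of Table 1, state that controls are drawn at random within the same hospital (or at least the same country) and the same birth weight range as the case. In Statistical Analysis, state that the respiratory AUC and association measures are estimated within site or country, that the stratum estimates are combined, and that the country results are shown side by side.

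This is a small change to control selection plus analysis wording. It needs no extra newborns or procedures, since controls come from the cohort. The price is slightly lower precision, and some matched sets may be harder to fill at small sites; there, match on country or adjust for site. The change does not correct misclassification of RDS within a hospital.

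A sensitivity analysis limited to newborns with a chest X-ray is not advised. X-ray is not among the study procedures in Table 1 and controls have no respiratory manifestations, so the restriction would probably exclude most controls.

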## Appendix

Multimedia Appendix 1 Data entry form.

## Abbreviations

GA: gestational age
RDS: respiratory distress syndrome
SGA: small for gestational age
TTN: transitory tachypnea of the newborn
WHO: World Health Organization
